**Outcomes and efficacy endpoints**

Both forms of treatment, EC plus polyacrylate dressing with or without pharmaceutical chlorite DAC N-055, are expected to be beneficial for the patient. However the reactive oxygen intermediate carrier, pharmaceutical sodium chlorite, which has been proven to enhance tissue regeneration and to exert antimicrobial effects, could also have a beneficial effect against the *Leishmania* parasite invader. This is to be checked as follows:

The time of complete wound healing is registered for each wound. After a maximum of 60 days of MWT the number of all healed wounds (complete epithelialization documented by photo) is registered versus the number of all wounds still open at that time. The parasite load is determined by limiting dilution analysis (see below) in a 2nd skin biopsy taken after complete healing or on day 61 after EC, if the wound has not healed completely.

GMS plans a late control of the ACL patients after six months with photodocumentation, Giemsa smear and eventually a 3rd biopsy for LDA, if there is still a tissue infiltration but the Giemsa smear is Leishmania-negative and if the patient is willing to consent to this.

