**Interventions**

1. **Skin biopsies**

Two punch biopsies are taken from every patient under local anaesthesia, the first before EC, the second after complete wound healing. One half of the 2.0 mm diameter cylinder is transferred into tubes with *Leishmania* culture medium under sterile conditions for limiting dilution analysis (LDA) within 48 hours to the Department of Medical Microbiology and Hygiene of the University Hospital of Freiburg. The second half is fixed in formalin for histopathology in Freiburg. For their second punch biopsy the patients will be examined in clusters. The second punch biopsy should be done within one week after complete healing to avoid drop outs. From wounds which have not completely healed after 8 weeks of MWT, a second biopsy will also be taken the following day.

1. **Electrocauterisation (EC)**

After intensive skin cleaning with water / soap first followed by rinsing with 70% ethanol and disinfection of the intact skin in both groups **A** and **B** with a 5% dilution of 4.5% (w/w) pharmaceutical chlorite plus 1.5 vol% acetic acid for 20 minutes, the nodule is locally anesthetized with 1% lidocaine. The whole nodule area is then electrocautered with a high-frequency electrosurgical Mini Cutter (HMC 80 HF Chirurgie) produced by Hüttinger Medizintechnik (D-79224 Umkirch) first using monopolar superficial coagulation and then monopolar deep coagulation for thermo-therapy starting with intensities from 4 to 6 depending on the thickness of the epidermis and using a broad blade and intensities between 5 and 7 after the skin has been opened.

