**Amendments to the original study protocol from June 12, 2004**

Amendment 1 (requested by the Ethics Committee of the University of Freiburg on July 28, 2004; submitted August 11, 2004; approved August 24, 2004): Informed consent of the patients

The patients will be informed orally by the doctors or the medical student about the planned diagnostic and therapeutic procedures. Specifically, they will hear about the advantages (e.g. more rapid cure, less infections, healing of the skin plus killing of the parasites) as well as the possible side effects of the new treatment (e.g. allergic reaction to the foil or the pharmaceutical chlorite) as compared to the established standard methods.

Amendment 2 (requested by the Ethics Committee of the University of Freiburg on July 28, 2004; submitted August 11, 2004; approved August 24, 2004):

Sample size and power calculation, randomization, primary and secondary endpoints

For this study, 100 patients shall be recruited, 50 in each treatment arm, eventually for technical feasibility reasons in a sequential order, 2 x 25 patients during the first 2 months and 2 x 25 patients during the following 2 months.

*Randomization* will be performed in two strata: patients with a single lesion and those with multiple lesions. In the latter case, one target lesion will be determined in advance for the primary evaluation; other lesions will be documented for further investigations.

*Primary endpoint* is the time until complete wound healing. Under the assumption that the median healing time is 4 weeks in the control arm and 2 weeks in the investigational arm and that the follow-up time is 60 days, a number of 40 patients each is necessary to obtain a power of 80% (significance level 5%). A presumed drop-out rate of 20% leads to the total number of 100 patients. Comparison of the study arms will be performed in the ITT population by means of the Log-rank test. Depending on the data, a more detailed analysis in a Cox Model including single/multiple lesions and parasite load at baseline as additional effects might be performed.

As a *secondary endpoint*, parasite load after 60 days will be compared in the PP population between the two study arms either by means of the Mann-Whitney-Wilcoxon test or in case that the distribution shows a singularity at zero, by means of the fourfold table chi-square test (dichotomized neg/pos).

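### The secondary endpoint is named as a day-60 parasite load, but most patients are biopsied at healing, so the arms would be sampled at different times after electrocauterisation

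*Combined protocol and SAP*

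**What the plan says.** - **Endpoint (Amendment 2).** For the one secondary endpoint that it names, "parasite load after 60 days will be compared in the PP population between the two study arms". The test is Mann-Whitney-Wilcoxon or, if values pile up at zero, a chi-square test on negative versus positive. Biopsy day does not enter either test.
- **Schedule (Interventions, Skin biopsies).** "Two punch biopsies are taken from every patient under local anaesthesia, the first before EC, the second after complete wound healing". Also: "The second punch biopsy should be done within one week after complete healing to avoid drop outs".
- **Schedule (Outcomes and efficacy endpoints).** Load is determined "in a 2nd skin biopsy taken after complete healing or on day 61 after EC, if the wound has not healed completely".
- **Unhealed wounds.** The Interventions section gives a different rule from the day 61 just quoted: "From wounds which have not completely healed after 8 weeks of MWT, a second biopsy will also be taken the following day".
- **Planning values (Amendment 2).** Patients are followed for 60 days, and the sample size rests on this assumption: "the median healing time is 4 weeks in the control arm and 2 weeks in the investigational arm".

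Amendment 2 is operative text that adds the endpoints. It does not alter the biopsy schedule. Nothing else supplies a load at a common time: the six-month biopsy is optional and selective, and the weekly smears are read only for presence of amastigotes.

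**The concern.** A healed patient has no sample at day 60, so the endpoint as named cannot be measured in most patients. What is measured is the load at a time set by the primary outcome, and the trial is powered on the assumption that this outcome differs twofold between arms. If chlorite works as hoped on wound closure, its patients are biopsied sooner after EC.

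The Outcomes section presents this biopsy as the check on whether chlorite acts against the parasite, and it is the only between-arm parasite comparison that the plan specifies. At stake is a wrong conclusion in either direction: an apparent disadvantage that reflects earlier sampling, or an apparent equality that reflects sampling both arms at the same stage of healing.

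**Working it through.** **1. Does a simple healing model fit the plan?** Inputs from Amendment 2: medians 28 and 14 days, follow-up 60 days, power 80%, level 5% (taken as two-sided), 40 per arm. Exponential healing is my assumption; it gives a hazard ratio of 28/14 = 2.

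- Healed by day 60: 1 − 2^(−60/28) = 77.4% control; 1 − 2^(−60/14) = 94.9% chlorite; mean 86.1%.
- Schoenfeld formula: 66 events, 66/0.861 = 76.6 patients, 38.3 per arm.
- Freedman formula: 71 events, 71/0.861 = 82.4 patients, 41.2 per arm.
- Drop-out: 80/(1 − 0.20) = 100.

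Both formulas lie within two patients of the stated 40 per arm, so the model is consistent with the plan.

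**2. When is the second biopsy taken?** With λ = ln 2/median and q = 2^(−60/median), the mean biopsy day is (1 − q)/λ + q if taken on the day of healing (day 61 if unhealed). A full one-week delay adds 7(1 − q).

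| | Control | Chlorite | Gap |
|---|---|---|---|
| Sampled on day 61 (q) | 22.6% | 5.1% | |
| Median biopsy day, no delay | 28 | 14 | 14 |
| Median biopsy day, 7-day delay | 35 | 21 | 14 |
| Mean biopsy day, no delay | 31.5 | 19.2 | 12.3 |
| Mean biopsy day, 7-day delay | 36.9 | 25.9 | 11.0 |

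Across both arms, (22.6 + 5.1)/2 = about 14% would have a day-61 sample.

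**3. What could this do to the test?** The documents give no rate of parasite decline, baseline load or assay variance, so this step is illustrative. Assumptions: no drug effect on parasites; the same log-linear decline in both arms, independent of healing; baseline 4 log10 with SD 1; detection limit 1 log10; biopsy 0 to 7 days after healing; 40 per arm. Simulated rejection rates at the 5% level:

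| Assumed half-life (days) | Mann-Whitney | Chi-square |
|---|---|---|
| 3 | 56% | 59% |
| 5 | 52% | 46% |
| 7 | 40% | 24% |
| 14 | 17% | below 1% |
| 28 | 8% | below 1% |

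Under these assumptions the faster-healing arm looks worse: at a 5-day half-life, 70% of control and 87% of chlorite samples are positive. The chi-square rate falls away at long half-lives because nearly every sample is positive. It also falls with very fast clearance, to about 27% at 1 day and 11% at half a day. With one common biopsy day (day 61 for illustration), the Mann-Whitney rate is 4–6% for half-lives of 5 to 28 days and about 0% at 3 days, where almost all samples are negative.

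**4. The two rules for unhealed wounds.** Counting moist wound treatment from the day of EC, the day after 8 weeks is day 57, against day 61. Unhealed at day 56: 2^(−56/28) = 25% control and 2^(−56/14) = 6.25% chlorite. Expected to heal between days 56 and 60: 25.0 − 22.6 = 2.4% and 6.25 − 5.13 = 1.1%, or about 0.9 and 0.4 of 40 patients.

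**The case against.** **Load at healing is a legitimate question.** Whether closed lesions are free of parasites matters, and biopsy day is a consequence of treatment, not a baseline imbalance. The arms can therefore be compared on it, subject to the usual caution about a per-protocol population. This stands. A reader might infer that the comparison is confounded and worthless; the documents do not support that. The fault lies in the label and in what would be read from it.

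**The direction is not known.** A reader might infer that the bias must run against chlorite. That needs load to fall with time since EC independently of healing. The Background gives some support for a fall: smears turned negative within 7 days in lesions given EC and the chlorite gel. It gives no decay rate and does not separate clearance from healing. If wounds close when parasites clear, sampling at healing pulls the arms together. This stands.

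**A fixed day-61 biopsy for everyone is not a clear improvement.** It looks like the obvious correction. But the Interventions section ties the biopsy to healing to limit drop-out, and the Background cites 36.2% loss over 3 months in an earlier Kabul trial. At the medians, patients would have to return 61 − 14 = 47 days (chlorite) or 61 − 28 = 33 days (control) after healing. The healed patients at risk of loss make up 95% of one arm and 77% of the other, so missing samples would again depend on healing. This stands.

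**The weekly smears are no clean substitute.** They come from wound edges and show only presence or absence. Under the same model, 29% of chlorite and 16% of control wounds are healed by week 1, and 50% and 29% by week 2. The Background also reports smear-negative lesions that were still positive on limiting dilution, in ulcers not pre-treated by EC.

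**Harm to the primary endpoint is slight.** A reader might infer that a day-57 biopsy spoils the healing endpoint. The documents do not say that a 2 mm punch delays closure, and about one patient per arm or fewer would be affected.

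**Conclusion.** The mismatch between endpoint and schedule is certain; it follows from the text alone. Its size in sampling time (about 23% against 5% sampled on day 61, and a mean gap of 11 to 12 days) rests on the plan's medians and on exponential healing. The gap arises only if chlorite speeds healing as assumed.

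The effect on the test is conditional. If load declines independently of healing, the false-positive rate for an antiparasitic difference at a common time runs from below 1% (chi-square, slow decline) or about 8% (Mann-Whitney, 28-day half-life) to over 50%, against the faster-healing arm. If healing tracks clearance, the arms are drawn together.

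This should be fixed, but it is not critical: it concerns the secondary endpoint, and the primary log-rank analysis is essentially unaffected.

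**What to change.** 1. In Amendment 2, rename the endpoint as parasite load at healing or, if unhealed, at end of treatment.
2. State that an arm difference, or its absence, is not by itself evidence about antiparasitic effect at a common time after EC.
3. Report the distribution of biopsy day by arm, and pre-specify a sensitivity analysis that takes biopsy day into account. Note with it that biopsy day is itself affected by treatment, so adjustment is not a full remedy.
4. Reconcile the Interventions section, the Outcomes section and Amendment 2 on the biopsy day for unhealed wounds.
5. Treat the weekly smears as supportive only.

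The cost is wording and one extra analysis, with no added visits or biopsies. A common sampling day is an option for the sponsor to weigh: it would remove the timing gap, at the risk of losing healed patients unequally between arms. That choice has to be made before sampling starts, because a missed common-time biopsy cannot be recovered.

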**Laboratory and parasitological studies**

1. **Wound smears** are taken weekly from the wound edges and analysed in the GMS laboratory to follow the development of the parasitological disease: The slides are dried, fixed with methanol, stained with Giemsa and then examined under the microscope at x100 magnitude for presence of the *Leishmania* amastigotes.
2. **Limiting dilution analyses** **(LDA)** are done to determine the parasite load per g of biopsy tissue in the Department of Medical Microbiology and Hygiene of the University Hospital of Freiburg, Germany, according to the method established in the laboratory of [name]. [name]. It is intended that the biopsies are subjected to analysis within 2-4 days after biopsy transfer into *Leishmania* medium avoiding exposure to temperatures above 25°C. For LDA, the biopsy sample will be minced and subjected to serial 2-fold dilutions (total number of dilutions = 15 ranging from undiluted to 1:32,768, number of wells per dilution step = 12) in modified Schneider´s Drosophila insect medium . The cultures are kept for a minimum period of 10 days, after which they are evaluated microscopically for the growth of *Leishmania* promastigotes. The number of parasites is estimated using Poisson statistics and the 2 minimization method .
3. **The determination of the parasite species** is done by PCR and restriction fragment length polymorphism analysis .

**Statistical analysis**

Statistical tests will be carried out according to standard methods as advised by the Department of Medical Biometry and Statistics, University of Freiburg.

**Amendments to the original study protocol from June 12, 2004**

Amendment 1 (requested by the Ethics Committee of the University of Freiburg on July 28, 2004; submitted August 11, 2004; approved August 24, 2004): Informed consent of the patients

The patients will be informed orally by the doctors or the medical student about the planned diagnostic and therapeutic procedures. Specifically, they will hear about the advantages (e.g. more rapid cure, less infections, healing of the skin plus killing of the parasites) as well as the possible side effects of the new treatment (e.g. allergic reaction to the foil or the pharmaceutical chlorite) as compared to the established standard methods.

Amendment 2 (requested by the Ethics Committee of the University of Freiburg on July 28, 2004; submitted August 11, 2004; approved August 24, 2004):

Sample size and power calculation, randomization, primary and secondary endpoints

For this study, 100 patients shall be recruited, 50 in each treatment arm, eventually for technical feasibility reasons in a sequential order, 2 x 25 patients during the first 2 months and 2 x 25 patients during the following 2 months.

*Randomization* will be performed in two strata: patients with a single lesion and those with multiple lesions. In the latter case, one target lesion will be determined in advance for the primary evaluation; other lesions will be documented for further investigations.

*Primary endpoint* is the time until complete wound healing. Under the assumption that the median healing time is 4 weeks in the control arm and 2 weeks in the investigational arm and that the follow-up time is 60 days, a number of 40 patients each is necessary to obtain a power of 80% (significance level 5%). A presumed drop-out rate of 20% leads to the total number of 100 patients. Comparison of the study arms will be performed in the ITT population by means of the Log-rank test. Depending on the data, a more detailed analysis in a Cox Model including single/multiple lesions and parasite load at baseline as additional effects might be performed.

As a *secondary endpoint*, parasite load after 60 days will be compared in the PP population between the two study arms either by means of the Mann-Whitney-Wilcoxon test or in case that the distribution shows a singularity at zero, by means of the fourfold table chi-square test (dichotomized neg/pos).

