As an alternative to the SbV treatment, the GMS started to treat fresh ACL nodules with **electrocauterisation (EC)** on a pilot basis since the beginning of 2003, as it was believed that such heat treatment could reduce the number of parasites allowing the immune system to cope with the remaining protozoa in a more efficient manner. Limiting dilution analyses carried out at the Department of Medical Microbiology and Hygiene, University Hospital of Freiburg, showed that the *Leishmania* parasites were still present in the tissue when the punch biopsy was taken under local anaesthesia shortly after EC before starting moist wound treatment (MWT).

Interestingly in 2004, the Dutch NGO in Kabul, HEALTH*Net* International, which cooperates with the London School of Hygiene & Tropical Medicine, filed a final report on a randomised controlled trial to test the efficacy of thermotherapy (TT) at 50 °C (TT without cauterisation) against *Leishmania tropica* versus intralesional and systemic SbV therapy. Based on Giemsa smears with PCR confirmation of Leishmania etiology in 10% of the enrolled patients, they found that TT (69.4 % cure rate after 3 months, mean duration to cure 43.46 days) was as effective as intralesional SbV (75.3 % cure rate after 3 months, mean duration to cure 58.9 days) and more effective than i. m. SbV (44.8% cure rate after 3 months, mean duration to cure 49.46 days). They enrolled 406 patients, but their total drop out rate during a follow-up period of 3 months was 36.2 % in Kabul.

When the GMS subsequently treated the EC wounds of their patients with 0.045% DAC N-055 containing hydrogel, this led to a complete epithelialization of the majority of lesions with depigmentation and edge flattening mostly within 4 weeks. Giemsa smears, which were found to be *Leishmania*-positive before EC, turned *Leishmania*-negativewithin 7 days and stayed negative until complete healing. The punch biopsies of two of such lesions were transported from Kabul to Freiburg within 48 hours in *Leishmania* growth medium, where they were subsequently found *Leishmania*-negative in limiting dilution analyses. However, in chronic ulcers which had not been pre-treated by EC, in some cases a discrepancy was found between Giemsa smears which had turned *Leishmania*-negative and limiting dilution analyses which remained *Leishmania*-positive.

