**C. Moist wound treatment and wound dressings**

0.5 ml of 4.5% (w/w) pharmaceutical chlorite solution per 50 g jelly (which equals a concentration of 5 mM NaClO2) pH 7 and drug free jelly pH 7 are freshly prepared in the GMS laboratory every day according to the attached “mucilago” formulation. The pots with the hydrogels are marked jelly A and B without any further indication for the personnel doing the wound dressing. The jellies are applied directly to the wounds with a sterile syringe, which are then covered with gauze and closed with a layer of food preservative folia fixed with a bandage, after the whole skin area covered by folia has been intensively cleaned with 70% ethanol. Dressings are renewed every day with a weekly pause on Fridays. The wounds are checked for possible superinfections by Giemsa-stained wound smears. If dry gauze dressing for one day does not change the situation, systemic antibacterial treatment is given. Anti-leishmanial and topical co-medication is not allowed. If a patient is over-due for his daily dressings for more than two days, he/she is excluded from the trial.

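### The 20% drop-out allowance has no source, and the rule excluding patients overdue for dressings conflicts with the ITT log-rank test on which the power depends

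*Combined protocol and SAP*

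**What the plan says.** Amendment 2 sets the sample size for time to complete wound healing. It assumes that "the median healing time is 4 weeks in the control arm and 2 weeks in the investigational arm". With 60 days of follow-up, it arrives at 40 patients per arm for 80% power at a 5% significance level. It continues: "A presumed drop-out rate of 20% leads to the total number of 100 patients". Accordingly, "100 patients shall be recruited, 50 in each treatment arm". On the analysis: "Comparison of the study arms will be performed in the ITT population by means of the Log-rank test". A PP population is named only for the secondary endpoint, parasite load. Neither population is defined, and no censoring rule is given.

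Two other places bear on this:

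- The Background describes an earlier thermotherapy trial with 406 enrolled patients and reports that "their total drop out rate during a follow-up period of 3 months was 36.2 % in Kabul".
- The section on moist wound treatment and wound dressings (Interventions, C) has dressings renewed daily except Fridays and adds: "If a patient is over-due for his daily dressings for more than two days, he/she is excluded from the trial".

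The inclusion and exclusion criteria leave out women and children partly to limit drop-outs. The plan nowhere compares its 20% with the 36.2%.

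**The concern.** There are two linked difficulties.

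First, the 20% is presumed, while the one observed rate in the documents, from the same city and disease, is higher. The 3 of 87 and 3 of 24 in the study design section are relapses, so they give no support to a drop-out rate.

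Second, the documents disagree about what happens to a patient who misses dressings. An ITT log-rank test keeps every randomised patient. Exclusion from the trial, read literally, takes some of them out after randomisation. Missing dressings may well be related to how the wound is doing, so removal can bias the comparison in a direction that cannot be predicted. It also turns each such patient into a complete loss of information, which is how the inflation from 40 to 50 per arm treats drop-outs. The trial is meant to isolate the effect of the chlorite, so a null result would be read against the declared 80% power.

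**Working it through.** **Inputs from the documents.** Median healing 28 and 14 days, follow-up 60 days, 80% power, 5% level, 50 per arm, 20% drop-out (all Amendment 2); 36.2% drop-out over 3 months (Background).

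**Assumptions.** Exponential healing times, so the hazard ratio for healing is 28/14 = 2. Two-sided 5%: the plan does not state the sidedness, but a one-sided test would need only 30 to 33 per arm, which does not match 40. Drop-out is the same in both arms and independent of healing.

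**1. The plan's own figure.**

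- Healed by day 60: 1 − 2^(−60/28) = 0.774 and 1 − 2^(−60/14) = 0.949; mean 0.861.
- Schoenfeld: 4(1.960 + 0.842)²/(ln 2)² = 65.3, so 66 events; 66/0.861/2 = 38.3 per arm.
- Freedman: (1.960 + 0.842)² × (3/1)² = 70.6, so 71 events; 71/0.861/2 = 41.2 per arm.

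The stated 40 lies between the two, and 40/0.80 = 50 per arm. The arithmetic is sound.

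**2. The Kabul rate over 60 days.** Linear: 36.2% × 60/90 = 24.1%. Constant hazard: 1 − 0.638^(60/90) = 25.9%.

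**3. Power if drop-outs are removed.** Events E = 100(1 − d) × 0.861. Power is Φ(√E × ln 2/2 − 1.960) by Schoenfeld and Φ(√E/3 − 1.960) by Freedman.

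| Drop-out d | Patients left | Events | Schoenfeld | Freedman |
|---|---|---|---|---|
| 20% | 80.0 | 68.9 | 82% | 79% |
| 24.1% | 75.9 | 65.3 | 80% | 77% |
| 25.9% | 74.1 | 63.8 | 79% | 76% |
| 36.2% | 63.8 | 54.9 | 73% | 70% |

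Simulated log-rank tests with 40, 37 and 32 per arm give about 82%, 79% and 73%, in line with Schoenfeld.

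**4. Power if drop-outs stay in, censored when they leave (50 per arm).** Let λ = ln 2/median.

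- *Evenly spread loss:* drop-out hazard μ = −ln(1 − d)/60. The probability of an observed healing is λ/(λ + μ) × [1 − exp(−60(λ + μ))].
- *Early loss:* a fraction d leaves at a uniform time in days 0 to 14. The probability is (1 − d)(1 − e^(−60λ)) + d[1 − (1 − e^(−14λ))/(14λ)].

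| Drop-out d | Even: events | Schoenfeld | Freedman | Early: events | Schoenfeld | Freedman |
|---|---|---|---|---|---|---|
| 20% | 80.2 | 87% | 85% | 73.2 | 84% | 81% |
| 24.1% | 78.9 | 87% | 84% | 70.6 | 83% | 80% |
| 25.9% | 78.3 | 87% | 84% | 69.4 | 82% | 79% |
| 36.2% | 74.8 | 85% | 82% | 62.8 | 78% | 75% |

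Simulated log-rank tests agree with the Schoenfeld columns to within about one point.

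**5. What drives the difference.** At 36.2% loss, keeping rather than removing the patients raises power from 73% to 85% if losses are even, and to 78% if they are all early (Schoenfeld). With the patients removed, raising the drop-out rate from 20% to 25.9% costs only three points. The handling of these patients therefore matters at least as much as the choice of rate.

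**The case against.** The strongest defence is that nothing here shows 20% to be too low. The 36.2% covers 3 months in a trial of other treatments, whereas this one follows men aged 18 or over for 60 days. The endpoint also helps: a patient lost after healing has already supplied the event. At a constant 36.2% per 90 days, 14.0% of controls and 8.8% of the chlorite arm would be lost before healing, a mean of 11.4%, which is below 20%. Dividing by 0.8 is a customary inflation and not an analysis rule; the rule is the ITT log-rank test, under which drop-outs normally count until censored. The exclusion of overdue patients may have been meant only to end study treatment or to define the PP set.

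Most of this stands. It rules out a stronger reading that someone might take from the figures: that the stated 80% is really 73%, or that enrolment should rise to 40/0.638, or 63 per arm. That reading needs the unscaled 3-month rate together with no data at all from drop-outs. The 73% is also a Schoenfeld value whose own starting point is 82%; scaled from exactly 80%, the figure would be about 71%.

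The defence does not settle how overdue patients are handled. It relies on keeping them in the test, and the dressing section says they are excluded from the trial. Nothing in the documents limits that exclusion to treatment or to the PP set. How many losses the rule would add is unknown, and they may overlap with ordinary drop-outs.

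**Conclusion.** The concern holds in a limited form. The sample-size arithmetic is correct, and the documents do not show the trial to be underpowered: at the rescaled Kabul rate, power is 76–80% even if drop-outs contribute nothing. What remains is an unsourced 20% beside an unmentioned 36.2%, and an unresolved conflict between the dressing section and the ITT analysis.

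Over drop-out of 20% to 36.2%, power runs from 79–82% down to 70–73% if these patients are removed (Freedman to Schoenfeld). If they are kept and censored, it is 85–87% with even loss and 78–84% with early loss by Schoenfeld, or 82–85% and 75–81% by Freedman. All of this rests on exponential healing, a hazard ratio of 2, a two-sided 5% level and drop-out unrelated to healing. The early-loss pattern is a stress case that the documents do not suggest. The risk of bias from removing patients after randomisation remains whatever the power.

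**What to change.** Reconcile the dressing section with Amendment 2 by stating that every randomised patient who stops or misses dressings remains in the ITT log-rank test. Day-60 healing status should be collected wherever obtainable; otherwise the patient is censored at the last visit. Where day-60 status shows healing on an unknown date, fix one dating convention in advance for both arms.

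Beside the 20% in Amendment 2, cite the 36.2% with its 3-month period, say why a lower figure is expected, and give the power of 100 patients over that range with drop-outs removed and with drop-outs censored.

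The cost is a few sentences and some effort to trace patients at day 60. The lower end of the stated power range will look less favourable. Enrolment, endpoint, test and dressing rule are unchanged; only the place of overdue patients in the analysis is clarified.

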**Methods**

**Study location**

The clinical study will be carried out at the GERMAN MEDICAL SERVICE (GMS), Darwaze-e Lahory (DL) clinic, in Kabul, Afghanistan. The clinic has been operating for more than two decades. Being mainly involved in leprosy and tuberculosis programs, the DL clinic also focuses on dermatological patients. 23.5% of all patients seen in 2003 presented with cutaneous leishmaniasis. Recently, the DL clinic has accumulated a lot of experience in moist wound care management with dressings and digital photo documentation of as many as 50 patients per day.

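### Size of the target lesion, a plausible predictor of healing time, is neither recorded nor included in the optional Cox model

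*Combined protocol and SAP*

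**What the plan says.** Amendment 2 (in the section on amendments to the protocol of June 12, 2004) states that the primary endpoint "is the time until complete wound healing". The arms are compared in the ITT population by the log-rank test, without covariates. Randomisation is stratified by single versus multiple lesions. Patients with several lesions have one target lesion fixed in advance. The only covariate-adjusted analysis is conditional on the data: "a more detailed analysis in a Cox Model including single/multiple lesions and parasite load at baseline as additional effects might be performed".

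Under Interventions, the electrocauterisation (EC) paragraph says: "The whole nodule area is then electrocautered". The eligibility text under Study design requires non-ulcerated lesions but sets no size limit. Size is not a stratum, a covariate or part of the target-lesion rule, and no section provides for measuring it. The Statistical analysis section only refers to standard methods on departmental advice.

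On photography, Study location credits the clinic with experience in "digital photo documentation of as many as 50 patients per day". Within the trial, Outcomes and efficacy endpoints asks for photos of complete epithelialisation and at the six-month control. It does not ask for a scaled photo at baseline.

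**The concern.** The endpoint is closure of a wound that the trial itself makes, and its starting extent follows the nodule. With no size limit at entry, that extent may differ considerably between patients. The two named covariates do not stand in for it. Single/multiple counts lesions and does not describe the target wound. Parasite load is a density per gram of biopsy tissue (Laboratory and parasitological studies), taken from half of a 2 mm punch.

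In a Cox model, leaving out a prognostic covariate pulls the treatment hazard ratio toward 1 and costs power even when the arms are balanced. In any single trial of this size the arms may also differ in lesion size by chance. If size was not recorded before EC, that difference cannot be examined afterwards. Finally, an adjusted analysis that may or may not be run, depending on the data, carries less weight than one fixed beforehand.

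**Working it through.** **1. Reproducing the plan's sample size.** Inputs from Amendment 2: "the median healing time is 4 weeks in the control arm and 2 weeks in the investigational arm"; "the follow-up time is 60 days"; 80% power; 5% significance. Two-sided testing and exponential healing times are assumptions, as neither is stated.

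- Hazards: ln 2/28 = 0.0248 and ln 2/14 = 0.0495 per day, so the hazard ratio (HR) for healing is 2.
- Healed by day 60: 1 − exp(−60 × ln 2/28) = 77.4% and 1 − exp(−60 × ln 2/14) = 94.9%; mean 86.1%.
- Schoenfeld: 4 × (1.960 + 0.842)² / (ln 2)² = 65.3, so 66 events; 66/0.861 = 76.6 patients, 39 per arm.
- Freedman: (1.960 + 0.842)² × (3/1)² = 70.6, so 71 events; 71/0.861 = 82.4 patients, 42 per arm.
- Dropout: "A presumed drop-out rate of 20% leads to the total number of 100 patients"; 80/(1 − 0.20) = 100.

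The stated 40 per arm lies between the two formulas. One-sided 5% gives 31 and 33 per arm and does not reproduce it.

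**2. Effect of adding size to the Cox model.** Simulation with 80 patients, 4,000 runs per setting, two-sided 5%; Wald tests for the Cox models. Monte Carlo standard error is about 0.6 points near 80% power (√(0.8 × 0.2/4000)). The plan's model contains treatment, single/multiple and parasite load; the comparison adds standardised log size. Assumptions: normal log size, no effect of lesion stratum or parasite load in their own right, no dropout among the 80. The strength of the size effect is not in the documents and is varied.

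(a) Healing times exactly as designed (exponential, overall HR 2), with size correlated r with healing time:

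| r | Log-rank | Plan's Cox | Plus size | Gain (points) |
|---|---|---|---|---|
| 0 | 81.4% | 80.6% | 80.2% | −0.4 |
| 0.2 | 81.4% | 80.4% | 81.1% | 0.7 |
| 0.3 | 81.4% | 80.2% | 83.4% | 3.2 |
| 0.4 | 80.4% | 79.3% | 85.4% | 6.1 |
| 0.5 | 81.5% | 81.0% | 90.1% | 9.1 |
| 0.6 | 81.8% | 80.4% | 92.7% | 12.3 |

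(b) Medians kept at 28 and 14 days and HR 2 at any given size, with the log hazard of healing falling by β per SD of log size. Size here adds spread beyond the exponential:

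| β | Log-rank | Plan's Cox | Plus size | Gain (points) | HR, plan's Cox | HR, plus size |
|---|---|---|---|---|---|---|
| 0 | 82.5% | 81.8% | 81.0% | −0.8 | 2.05 | 2.07 |
| 0.25 | 77.3% | 76.9% | 79.9% | 3.0 | 1.99 | 2.06 |
| 0.5 | 68.8% | 68.0% | 78.7% | 10.7 | 1.87 | 2.05 |
| 0.75 | 57.7% | 56.8% | 76.6% | 19.8 | 1.73 | 2.05 |
| 1.0 | 47.1% | 46.5% | 74.6% | 28.1 | 1.64 | 2.06 |

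HRs are medians over runs. With no treatment effect, rejection rates were 5.6–6.1% for the plan's Cox model and 5.3–6.0% with size, so the gain is not bought with extra false positives.

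**3. If parasite load tracks size.** In (b) at β = 0.75, the gain falls from 19.8 points to 15.7 at a load–size correlation of 0.5 (61.1% to 76.8%) and 8.1 at 0.8 (69.4% to 77.5%).

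**4. Chance imbalance.** With 50 per arm, the standard error of the between-arm difference in standardised size is √(2/50) = 0.2 SD. A difference of about 0.4 SD (1.96 × 0.2 = 0.39) is exceeded in one direction or the other in about 5% of trials. At β = 0.5 it would shift the log HR by about 0.4 × 0.5 = 0.2, a factor of exp(0.2) = 1.22.

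**The case against.** The strongest reply is that the quoted model is optional and secondary. The trial's decision rests on the log-rank test, which randomisation keeps valid, and a short covariate list for a supporting model is a legitimate choice. This stands, and it limits the point.

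A reader might infer that the trial is underpowered, or that one ruler measurement would restore lost power to the primary comparison. The documents do not support either. The 40 per arm reproduces for the log-rank test, and a covariate in a Cox model beside that test leaves its power unchanged. The low log-rank figures in table (b) arise only because size is assumed to spread healing times beyond the exponential; in table (a) no planned power is lost. Primary power would change only if a size-adjusted or size-stratified analysis were itself made primary.

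It can also be said that no section states how strongly size affects healing, and that diameter does not capture the depth of cauterisation. Both are true. They make the gain conditional, but they do not remove the case for recording size.

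Nor should the existing arrangements be overread. The photography under Study location describes general clinic experience, and advance designation of a target lesion applies only to patients with several lesions. Measuring every patient is therefore a small addition, not something already in place.

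**Conclusion.** The point holds as a modest, inexpensive improvement. Lesion size is plausibly a strong predictor of the primary endpoint, it is absent from the whole plan, and the only adjusted analysis is left open until the data are seen.

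The gain in power of the adjusted analysis is about nil, or a loss of under 1 point, if size is not prognostic. It is about 1–3 points if weak (r 0.2–0.3, or β 0.25), 6–11 if moderate (r 0.4–0.5, or β 0.5) and 12–28 if strong (r 0.6, or β 0.75–1.0). It shrinks if parasite load tracks size. All of this rests on the assumed size effect and the simulation settings above.

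The adjusted HR describes the effect at a given lesion size, so it may lie further from 1 than the overall HR without either being in error. The benefit is a sharper supporting analysis and the ability to see and correct a chance imbalance. It is not a correction of the sample size or of the log-rank test.

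**What to change.** Record the largest diameter (mm) of the target lesion, or of the only lesion, in every patient before EC, by ruler or from a photo with a scale. Without such a record the size cannot be recovered later.

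Before unblinding, replace the data-dependent option in Amendment 2 with one pre-specified Cox model containing treatment, single/multiple lesions, baseline parasite load and log diameter. Report it as the planned adjusted analysis supporting the primary log-rank test. Parasite load stays in, since the plan already names it. Tabulate diameter by arm with the other baseline data.

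The cost is one case-report field per patient, a sentence or two of analysis text, and a negligible loss of precision if size proves not to be prognostic. No invasive procedure or extra staff is needed.
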